#### Secondary outcomes

Secondary outcomes include: changes in other biochemical and clinical metrics (specifically serum total cholesterol, serum triglycerides, serum low-density lipoprotein cholesterol, serum high-density lipoprotein cholesterol, estimated glomerular filtration rate and albumin:creatinine ratio, blood pressure, body mass index and waist circumference, as recorded in the GP patient record or patient’s local pathology laboratory); incidence of diabetes-related complications (specifically autonomic and peripheral neuropathy, peripheral arterial disease, diabetic foot ulceration, lower limb amputation, microalbuminuria, chronic kidney disease, proliferative and non-proliferative diabetic retinopathy, glaucoma, serious vision loss, acute state of severe uncontrolled diabetes requiring hospitalisation, myocardial infarction, stable and unstable angina, trans-ischaemic attack, cerebrovascular accident and sexual dysfunction); health-related quality of life (measured by the Assessment of Quality of Life - 4 Dimension [AQoL-4D] instrument); clinical depression (measured by the Patient Health Questionnaire); success of tailored care (assessed by the practitioner satisfaction survey, Patient Evaluation of the Quality of Diabetes Care survey, patient semi-structured interviews and practitioner focus groups); and economic sustainability (e.g., cost utility analysis). All outcomes are measured at baseline and will be measured again at the end of the trial (in approximately 18 to 22 months). Secondary outcome data will be sourced from patient and practitioner surveys (as outlined above), a patient diary, patient semi-structured interviews, practitioner focus groups, selected sections of the GP patient record imported into cdmNet, the Medicare Australia database (for Pharmaceutical Benefits Scheme and Medicare Benefits Scheme data), the National Diabetes Supply Scheme (NDSS) database, and hospital separation databases of the Queensland, Victorian and South Australian Departments of Health.

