## Background

Diabetes mellitus is a chronic metabolic disorder that poses a significant health care problem in both developed and developing countries around the world, including Australia. An estimated 366 million people are affected by diabetes worldwide, and the incidence and prevalence of diabetes continues to rise, with more than 552 million people expected to be affected by the disorder by 2030—an increase of 51 percent [1]. People with diabetes are at risk of developing a range of complications, including chronic renal disease, diabetic eye disease and cardiovascular disease [2]. The impact of diabetes on the health system is considerable (in terms of both financial and human resources), with four percent of hospitalisations, 3.7 percent of general practitioner visits and 7.2 million prescriptions in Australia in 2009–10 attributed to the condition [3]. Direct and indirect health care costs related to the management of diabetes in Australia were estimated at AU$3.1 billion (excluding Commonwealth benefits) for type 2 diabetes (in 2001–02) [4], and at least $430 million for type 1 diabetes (in 2004–05) [5]. The chronicity and prevalence of diabetes, and the complications associated with the disorder, mean that diabetes will become an increasingly large burden on the health system, and on society, if new and more effective ways to manage it are not identified.

Australia has a unique opportunity to find better ways of caring for people with diabetes. Despite clear clinical objectives, fewer than fifty percent of people diagnosed with diabetes achieve the recommended targets for glycosylated haemoglobin, blood pressure and blood lipids [6-11]. Although care planning has been shown to result in substantial improvements in clinical and process outcomes for people with diabetes [12], almost eighty percent of GPs believe that the current care planning system involves too much red tape [13]. As a result, only eighteen percent of people with diabetes complete the recommended annual cycle of care [14], and approximately seventy percent do not have a multidisciplinary care plan at all [15].

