### Interventions

Each general practice (cluster) is randomly assigned to one of the three treatment arms. Participants in the control group are assigned ‘usual care’, meaning that practices will continue to provide care as usual.

Practices assigned to Intervention 1 experience two changes: access to an online chronic disease management network (cdmNet) and access to training and capability building. The cdmNet decision support service is instrumental in generating, updating and reviewing multidisciplinary care plans; facilitating communication between team members; sharing patient information; engaging patients in their care; and facilitating service payments. The care plans generated by cdmNet in Intervention 1 are pre-populated with the minimum care requirements for the general diabetes population, as informed by best practice guidelines and recommended treatments for any recognised comorbidities. CdmNet also generates population-level clinical status reports that allow GPs to proactively manage their population of people with diabetes enrolled in the trial. The training and capability building has three main functions: to assist practices in implementing the new model of care and cdmNet; to provide regular access to endocrinologists/diabetologists; and to provide a forum where practices can find out about new developments in diabetes care and share their experiences with other trial participants.

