Practices assigned to Intervention 2 experience four changes: access to cdmNet; altered funding arrangements; the provision of a care facilitator; and access to training and capability building. Coordinated care is facilitated through the use of the cdmNet decision support service (as in Intervention 1), but with the addition of risk stratification. Patients are stratified into one of four risk categories based on whether they have complications associated with diabetes (e.g., peripheral neuropathy, background diabetic retinopathy, foot ulceration) and whether their diabetes is under control (uncontrolled diabetes requiring additional allied health services is defined as either HbA1c >7.5% [>58.5 mmol/mol], systolic blood pressure >150 mmHg, total serum cholesterol >5.0 mmol/l, or systolic blood pressure >140 mmHg plus total serum cholesterol >4.5 mmol/l). The four risk categories are characterised as follows: (1) not complex and within range; (2) complex and within range; (3) not complex and out of range; and (4) complex and out of range (see Figure 2). The care plan that is generated for the patient reflects the minimum care needs of individuals in their respective strata, as informed by best practice guidelines. Care in Intervention 2 is also coordinated through the provision of a full-time care facilitator (a tertiary-qualified health professional with experience in primary health care delivery), whose role is to assist the multidisciplinary team in delivering care in accordance with the agreed care plan. The care facilitator has a case load of approximately 300 to 400 patients across all four risk strata.

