**Figure 2 F2:**
[figure not shown]
**Overview of risk stratification categories**^**#**^**.** HbA1c = Glycosylated haemoglobin; SBP = Systolic blood pressure. ^#^These risk stratification categories apply to participants with type 2 diabetes. Participants diagnosed with type 1 diabetes will be provided with the same level of resources as persons in the ‘out-of-range/complex’ category. Newly diagnosed patients will receive the support designated from their category plus additional support for introductory needs.

The altered funding arrangements that are tested in Intervention 2 comprise three components: flexible funding for general practices; pay-for-performance payments for general practices; and flexible funding for allied health professionals. Flexible funding for general practices provides upfront, lump sum funding for all patients who are voluntarily enrolled in the trial at a given practice, which is adjusted according to the risk of the patient population. This funding is used to fund care planning activities for those patients who require it (and is paid once a patient is enrolled rather than for completion of any specific activities) but it does not replace usual GP consultation fees covered by Medicare (Australia’s universal healthcare system). Pay-for-performance payments reward practices for improvements in patient clinical outcomes, meeting pre-defined levels of positive patient experience and completing pre-defined clinical processes. Flexible funding for allied health professionals is accessed on a fee-for-service basis, drawing on a risk-adjusted allowance for each patient. Participants in the control group, Intervention 1 and Intervention 2 will receive their respective care for a period of approximately 18 to 22 months (depending on when they are risk stratified).

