#### Economic evaluation

Economic sustainability will be assessed by estimating the total mean per patient cost (including co-payment) and cost to government (separately for the Commonwealth and State governments) of patients in each of the three treatment groups. This will allow the DCP to estimate cost and budget impacts of the intervention models. Data will be sourced from Medicare Australia, State governments (for hospital in-patient, emergency and outpatient services), the patient diary and the NDSS. Depending on how well participants are matched across groups at baseline, some statistical adjustment may be necessary. Each person will be allocated to a diabetes disease stage (based on risk and morbidity profile), and the mean annual cost at each disease stage will be estimated across all three groups. The rate of progression in disease stage over the course of the study will be described for each patient and compared across groups to test for any between-group differences. If differences are detected, this will be used to model the downstream cost and budget implications of the three models of care.

A cost utility analysis will be conducted using the AQoL-4D to derive quality of life utility scores and to measure any change across the trial. Results for the three groups will be compared to identify any differential change in quality of life that can be multiplied by time to generate quality-adjusted life year (QALY) gain or loss for each intervention group. A quality of life utility score will be calculated for each disease stage (from persons in the disease stage), with a lower quality of life expected with more advanced disease. If a difference in the rate of disease progression is identified, this will be used to model the downstream impact on QALYs. The cost of implementing the model will be derived from trial administrative data and health care costs as described above. These costs will be combined with QALYs (within the trial and modelled beyond the trial) to estimate cost per QALY gain if it is found that the intervention is more expensive but delivers greater quality of life.

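### Test-detected complications are pooled with hard events as incidence, and arm-dependent detection may bias that comparison and the stage progression behind the cost and QALY model, in either direction

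*Protocol article*

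**What the plan says.** The Secondary outcomes section defines one complications outcome: "incidence of diabetes-related complications (specifically autonomic and peripheral neuropathy, peripheral arterial disease, diabetic foot ulceration, lower limb amputation, microalbuminuria", continuing through chronic kidney disease, retinopathy, myocardial infarction, angina, cerebrovascular accident and other items. It says that all outcomes are measured at baseline and again at the end. The sources it names are surveys, a patient diary, interviews and focus groups, parts of the GP record, Medicare and diabetes supply data, and state hospital separation data. It describes no complication examination common to all arms.

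The Interventions section sets out what differs by arm:

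- Control: "practices will continue to provide care as usual".
- Intervention 1: care plans are "pre-populated with the minimum care requirements for the general diabetes population".
- Intervention 2: "Coordinated care is facilitated through the use of the cdmNet decision support service (as in Intervention 1), but with the addition of risk stratification". The stratification uses complication status. This arm also has a care facilitator and a pay-for-performance scheme that rewards, among other things, "completing pre-defined clinical processes". The processes are not named.

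The Economic evaluation section assigns each patient a disease stage from risk and morbidity profile, and then: "The rate of progression in disease stage over the course of the study will be described for each patient and compared across groups". If a difference is found, it drives the modelled downstream costs and QALYs.

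**The concern.** Amputation, infarction, stroke and hospitalised uncontrolled diabetes come to notice however attentive the practice is. Early retinopathy and neuropathy usually enter a GP record because someone looked. How often practices look is part of what is randomised: guideline prompts go to both intervention arms and not to control. The Primary outcome section confirms that the care plan directs measurement, since it says so for HbA1c collection.

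A count of recorded new complications therefore mixes two effects, fewer complications arising and more being found. They can oppose each other, so an intervention that improves care might show no benefit, or apparent harm, on this outcome. The economic answer is exposed as well. A patient whose existing neuropathy is newly recorded may appear to have moved to a worse stage, and a between-arm difference of that origin would be projected forward as disease progression.

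**Working it through.** The article gives no complication rate, testing rate or power for this outcome, so there is no figure to reproduce. The calculation below illustrates how sensitive the comparison is.

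**Inputs from the article (Sample size calculation).** 1,250 patients and 50 practices per arm; 20% attrition, so 1,250 × 0.8 = 1,000 analysed per arm, or 20 per practice; ICC 0.05; stated design effect 3.45; two-sided alpha 0.025. With 20 analysed per practice the design effect would be 1 + (20 − 1) × 0.05 = 1.95, so both values are used.

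**Assumed inputs.** Share with an undetected complication at baseline, u = 5% to 20%; true new onset, i = 5%; probability s that a complication present during follow-up is found and recorded.

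**Model.** Recorded incidence = (u + i) × s. If u and i are equal in two arms, the recorded risk ratio is the ratio of the s values.

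**Step 1: no true effect.**

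- s = 50% v 65%: at u = 5%, 0.10 × 0.50 = 5.0% v 0.10 × 0.65 = 6.5%; at u = 20%, 12.5% v 16.25%. Recorded risk ratio 1.30 in both cases.
- s = 50% v 80%: at u = 5%, 5.0% v 8.0%; at u = 20%, 12.5% v 20.0%. Recorded risk ratio 1.60.

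**Step 2: chance of a significant false excess.** This is Φ(z − 2.24), with z = (p₂ − p₁) / √{[p₁(1 − p₁) + p₂(1 − p₂)] / (1,000/DE)}. Example at u = 5%, 50% v 65%, DE 3.45: effective n = 1,000/3.45 = 289.9; standard error = √[(0.0475 + 0.0608)/289.9] = 0.0193; z = 0.015/0.0193 = 0.78; Φ(−1.46) ≈ 7%.

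| Detection, control v intervention | Recorded risk ratio | DE 3.45 | DE 1.95 |
|---|---|---|---|
| 50% v 50% | 1.00 | 1.25% | 1.25% |
| 50% v 65% | 1.30 | 7–17% | 11–30% |
| 50% v 80% | 1.60 | 22–58% | 39–85% |

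The ranges run from u = 5% to u = 20%.

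**Step 3: a true benefit hidden.** If the true risk ratio of 0.8 applies to everything recorded, 0.8 × 1.25 = 1.00, so detection 1.25 times higher hides it. If the benefit acts only on new onset, less is needed: at u = i = 5%, (0.05 + 0.8 × 0.05)/0.10 = 0.90, and 1/0.90 = 1.11.

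**Step 4: reversal.** Suppose stratification in Intervention 2 finds existing cases at the start, so that u is 5% there and 10% in control. Control records (0.10 + 0.05) × 0.50 = 7.5%. Intervention 2 records (0.05 + 0.05) × 0.65 = 6.5%. The risk ratio is 6.5/7.5 = 0.87, an apparent benefit with no true effect and with better detection during follow-up.

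**The case against.** The strongest reply is that the plan measures every outcome at baseline and at the end in every arm. Estimated glomerular filtration rate and albumin:creatinine ratio are themselves listed outcomes, so microalbuminuria and chronic kidney disease should be ascertainable throughout. This stands in part, and it is why those two conditions are a lesser worry than retinopathy and neuropathy. It does not remove the problem. The sentence fixes timing, not method, and the values come from GP records or local laboratories, so missingness may still differ by arm.

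It may also be said that a condensed article leaves case definitions to a fuller document. That is accepted. The point here is the outcome, the sources and the economic use that the article does fix.

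Three stronger readings are tempting and are not supported:

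- A reader might infer that both interventions pay practices to look for complications. Intervention 1 stays within the current funding model. Only Intervention 2 has process payments, the processes are unnamed, and its flexible practice funding is not tied to specific activities.
- A reader might take the Background statement that "only eighteen percent of people with diabetes complete the recommended annual cycle of care" as the control detection rate. Against an assumed 50% in an intervention arm that would give 0.50/0.18 = 2.78. But it describes the whole cycle among people with diabetes generally. Any single test is done at least as often, and these are consented patients with planned baseline and end measurements.
- A reader might conclude that the interventions will appear to cause complications. Step 4 shows that the sign is not fixed.

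**Conclusion.** The concern holds as a risk of bias of unknown size and direction in a secondary outcome and in the economic model; the primary HbA1c comparison is not at issue here. What the documents establish is the structure: test-detected conditions pooled with hard events, largely routine sources, prompts that differ by randomised arm, and a morbidity-based stage that carries any difference forward. What they do not establish is the size. With assumed detection of 50% v 65%, the recorded risk ratio is 1.30 under no effect, with a 7–17% chance of a significant false excess at the stated design effect, against 1.25% under equal detection. A 1.25-fold difference in detection hides a true risk ratio of 0.8. These figures rest on assumed detection rates, prevalence and onset, and on borrowing the alpha set for the primary comparison. Hospital-recorded events are largely free of the problem, which is what makes a split workable.

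**What to change.** **Secondary outcomes.** Split the complications outcome. Base between-arm conclusions about complications on events ascertained alike in all arms from the hospital separation data, such as amputation, myocardial infarction, stroke and hospitalised uncontrolled diabetes. Report the test-detected conditions separately, as newly recorded diagnoses, beside the proportion tested in each arm at baseline and at the end. Assign every listed condition to one class before the data are seen.

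**Economic evaluation.** Keep the planned stage-progression analysis, since a stage built on risk and morbidity cannot rest on hospital events alone. Add a sensitivity analysis in which test-detected diagnoses do not drive a change of stage, and do not read a stage difference as disease progression if it disappears there.

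**Tested-at-both-times analysis.** If one is run, label it exploratory: the intervention affects who is tested, so it conditions on something that happens after randomisation.

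**Cost.** One extra table and one extra model run from data already planned, with no new assessments. The real price is that fewer events support the complication comparison, so it will be less precise.

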### Sample size calculation

A minimum sample size of 150 practices (or 50 practices per trial arm) and 3,750 patients (or 1,250 patients per trial arm) would allow a difference of 0.25 percentage points of HbA1c to be detected between any two trial arms with 80 percent power. The sample size is based a standard deviation of HbA1c of 1.4 percent, 20 percent attrition over 18 months, a design effect of 3.45 based on an ICC of 0.05 (correlation between baseline and 18-month HbA1c), and a two-sided alpha level set at 0.025 to adjust for pairwise comparisons.

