### Recruitment

Seven Medicare Locals/Divisions of General Practice (independent entities that are responsible for coordinating local primary health care services) [19] across the states of Queensland (n = 4), South Australia (n = 2), and Victoria (n = 1), Australia, are taking part in the trial. Prior to the commencement of the trial, each Medicare Local/Division of General Practice distributes study information sheets to all general practices (clusters) within their network and seeks expressions of interest to participate in the trial. Practices that express an interest in participating in the trial are enrolled in the project and randomly assigned to one of three treatment groups: control group, Intervention 1 or Intervention 2 (Figure 1). It is expected that fifty general practices will be enrolled in each group. Each enrolled practice is required to undergo training to familiarise themselves with the assigned intervention and study procedures. Medicare Locals/Divisions of General Practice that are assigned to Intervention 2 are supported by a ‘trial delivery and integration team’ to recruit and train care facilitators.

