### Randomisation

In four of the Medicare Locals/Divisions of General Practice, enrolled general practices are randomly allocated to the control group or Intervention 1 at a ratio of 1:2. In the other three Medicare Locals/Divisions of General Practice, practices are randomly assigned to the control group or Intervention 2 at a ratio of 1:2. A single type of intervention is tested in each Medicare Local/Division of General Practice as a result of two practical constraints: (1) care facilitators included in Intervention 2 are required to work with four or five practices within a single geographic area in order to work effectively; and (2) Medicare Locals/Divisions of General Practice would find it difficult to enrol and support practices using two different interventions, given that Intervention 1 and Intervention 2 comprise multiple components. Randomisation is applied after recruiting each group of three practices in a combined Medicare Local/Division of General Practice and Region stratum, where Region refers to urban or rural area. This helps to mitigate the potential bias created by testing only one intervention in each Medicare Local/Division of General Practice. Randomisation is applied separately for urban and rural practices within each Medicare Local/Division of General Practice because it is expected that service use and availability will differ by region. To approximate equality of sample sizes in each group, block randomisation is used with computer-generated, randomly permuted blocks of three. A researcher who is not involved in the implementation of the project and is blinded to the identity of the practices performs this task.

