### Statistical analysis

#### Main analysis

Descriptions of participants’ baseline characteristics (e.g., demographic data, comorbidities and clinical metrics) will be reported by treatment group. Categorical variables will be summarised by frequencies and percentages. Continuous variables will be summarised by means and SEMs, or non-parametric equivalents. All primary statistical analyses will be performed on an intention-to-treat basis. The continuous variable—HbA1c at approximately 18 to 22 months—will be compared between groups using a linear mixed effect model with adjustment for clustering and stratification status (Medicare Local/Division of General Practice and metro/rural practice location). The time/group interaction parameter will be used to formally test for an intervention effect. Secondary outcomes (excluding economic sustainability and value for money) will be analysed similarly. These findings will be presented in accordance with the reporting requirements outlined in the Consolidated Standards of Reporting Trials (CONSORT) statement - extension for cluster randomised trials [21].

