## Discussion

The DCP is designed to facilitate a robust yet pragmatic comparison of different, evidence-based models of care in order to evaluate how care can be improved for people with diabetes, and to determine the level of change that would be required to achieve this in the Australian context. Intervention 1 tests the extent to which current reforms (such as e-Health and clinical training initiatives) will improve care for people with diabetes. Intervention 2 tests the impact of altering primary care funding to create a ‘health care home,’ in which patients voluntarily register with a practice and are cared for by a multidisciplinary team coordinated by a care facilitator. Implementing the ‘health care home’ model of care (Intervention 2) at scale would involve substantial changes to the health system, and the DCP will therefore evaluate the incremental benefit of this intervention to ascertain if nationwide implementation is worthwhile.

A number of steps have been taken to ensure that this evaluation is rigorous and objective, and to increase the validity of the project’s final recommendations, including: introducing as much randomisation as is possible for this type of complex health reform; choosing populations to be representative of the Australian general practice landscape; and ensuring that the size of the trial will allow for testing of a range of different hypotheses (for example, whether the interventions work better in small or large practices and in urban or non-urban areas, and whether they affect people with more complicated diabetes and people with less complicated diabetes in different ways).

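### The 80% power claimed between any two arms treats every pair as 50 v 50 practices, but each intervention is randomised against only about 25 controls and the two interventions are never randomised against each other

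*Protocol article*

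**What the plan says.** The Sample size calculation gives "A minimum sample size of 150 practices (or 50 practices per trial arm) and 3,750 patients (or 1,250 patients per trial arm" and says that this "would allow a difference of 0.25 percentage points of HbA1c to be detected between any two trial arms with 80 percent power". The Primary outcome section repeats the claim for any pair of groups and calls 0.25 points clinically significant.

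The Randomisation section describes two separate allocations. In four Medicare Locals/Divisions, "enrolled general practices are randomly allocated to the control group or Intervention 1 at a ratio of 1:2". In the other three, "practices are randomly assigned to the control group or Intervention 2 at a ratio of 1:2". No Medicare Local hosts both interventions. Under Recruitment, "It is expected that fifty general practices will be enrolled in each group".

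The Main analysis uses a linear mixed model with "adjustment for clustering and stratification status (Medicare Local/Division of General Practice and metro/rural practice location", and names the time/group interaction as the formal test of effect. The Discussion acknowledges the one-intervention-per-area design as a drawback and says that the evaluation team will detect and correct bias between Medicare Locals. It says nothing about what that correction costs in power.

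**The concern.** A calculation with 50 practices on each side fits a trial in which all three arms are randomised together. Here the 50 controls fall into two sets of about 25, each randomised against one intervention only. Intervention 2 can be set against Intervention 1 in only two ways: through their separate control groups, or by comparing different Medicare Locals directly. None of the inputs listed in the Sample size calculation allows for this.

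The Discussion says that the trial will judge the incremental benefit of Intervention 2, to decide whether nationwide implementation is worthwhile. That is the contrast with the least randomised information. A null result read against a published 80% could be taken as evidence of no added benefit when the trial had little chance of finding one.

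**Working it through.** **Inputs (Sample size calculation unless noted).** Difference 0.25; "standard deviation of HbA1c of 1.4 percent"; two-sided alpha 0.025; power 80%; 1,250 patients and 50 practices per arm, so 25 patients per practice; 20% attrition, so 1,000 evaluable per arm; design effect 3.45; ICC 0.05. Allocation is 1:2 within each area (Randomisation) and 50 practices are expected per group (Recruitment). Normal quantiles: z(0.9875) = 2.2414 and z(0.80) = 0.8416, sum 3.083.

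**Step 1: the plan's own figure.** Unclustered n per arm = 2 × 1.4² × 3.083² / 0.25², which rounds up to 597. Then 597 × 3.45 = 2,060, and 2,060 / 0.8 = 2,575 per arm, against 1,250 stated. In the other direction, with 1,000 evaluable per arm the standard error is 1.4 × √(2 × 3.45/1,000) = 0.1163. Power = Φ(0.25/0.1163 − 2.2414) = 46%. The 80% does not reproduce.

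A design effect of 3.45 with ICC 0.05 implies 1 + (3.45 − 1)/0.05 = 50 patients per practice. At the planned 25 it is 1 + 24 × 0.05 = 2.2, and power for 50 v 50 is 67%.

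**Step 2: controls per intervention.** At 1:2, 50 Intervention 1 practices go with 25 controls, and 50 Intervention 2 practices with 25 others. The control total is 50, which agrees with Recruitment.

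**Step 3: variance of each contrast, taking one practice's variance as 1.**
- 50 v 50: 1/50 + 1/50 = 0.04
- Intervention v its own controls: 1/50 + 1/25 = 0.06, a ratio of 1.5
- Intervention 2 v 1 through separate controls: 0.06 + 0.06 = 0.12, a ratio of 3

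A least-squares fit with seven area fixed effects gives the same 0.06, 0.06 and 0.12. Without area effects it gives 0.04 for every pair.

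**Step 4: power if only within-area information counts.** With variance ratio k and the stated 80% granted for 50 v 50, power = Φ(3.083/√k − 2.2414) and the difference detectable with 80% power is 0.25 × √k.
- k = 1.5: Φ(0.276) = 61%; detectable 0.31
- k = 3: Φ(−0.461) = 32%; detectable 0.43

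**Step 5: the same from the stated inputs.** Replace 3.083 by 0.25/SE.

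| Design effect | 50 v 50 | 50 v 25 | Intervention 2 v 1 |
|---|---|---|---|
| 3.45 (as stated) | 46% | 31% | 16% |
| 2.2 (25 per practice) | 67% | 48% | 25% |

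**Step 6: dependence on how area is modelled.** Under a random area effect on the tested contrast, the answer depends on the between-area variance, which the article does not give. Assuming values for it as a multiple of one practice's variance, and granting 80% at zero:

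| Assumed multiple | Intervention v control | Intervention 2 v 1 |
|---|---|---|
| 0 | 80% | 80% |
| 0.1 | 71% | 51% |
| 1 | 63% | 35% |
| 5 | 61% | 33% |

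If area enters only as a main effect, constant over time, it cancels from each practice's change. The time-by-group test then compares 50 v 50 (variance 0.04) for every pair.

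**The case against.** The strongest reply is that the Main analysis does not say that Medicare Local is a fixed effect on the change, and it names no area-by-time term. Its formal test is the time/group interaction. With area main effects only, all 50 controls contribute and the split costs no power. This stands. A reader might infer that the trial's power simply is 61% and 32%, but the document does not support that. Those figures hold only if area differences in change are removed.

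The reply has a price, however. Keeping all 50 controls means comparing Intervention 1 practices partly with controls from Medicare Locals where Intervention 1 was never on offer, and that part is not randomised. Area differences in HbA1c change then remain uncorrected, contrary to the Discussion. The plan cannot claim both full correction and full 50 v 50 information.

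A second reply is that 61% and 32% start from an 80% that the inputs do not yield. This also stands, so they serve only to isolate the effect of the split. Gains from baseline adjustment might rescue the 80%: with design effect 2.2 and an assumed baseline-to-follow-up correlation of 0.5, 50 v 50 power is about 81%. The article states no such adjustment in the calculation, and the 1.5-fold and 3-fold ratios would still apply on top.

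A reader might also look for a power figure for the subgroup questions, since the Discussion speaks of "ensuring that the size of the trial will allow for testing of a range of different hypotheses". No single figure fits. Practice size and region vary between practices, whereas complexity of diabetes varies within them, and the article states no subgroup power to contradict. Nor does the point show that allocation should become 1:1 within areas. That would trade intervention practices for controls, and the 1:2 scheme serves the stated aim of similar group sizes.

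**Conclusion.** The point holds in conditional form. The claim of 80% power for any two arms is unsupported because it takes no account of the two-set randomisation.

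If Medicare Local differences in change are fully adjusted for, variance is 1.5 times the 50 v 50 value for each intervention v control and 3 times for Intervention 2 v 1. Granting the stated 80%, power is about 61% and 32%. With random area effects it lies between those values and 80%. At 80% the comparison is partly non-randomised. On the inputs as printed, the within-area figures are 31% and 16%, or 48% and 25% at design effect 2.2.

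These results assume the expected 50/50/50 enrolment, the 1:2 ratio in every area, and equal variance across practices. The ratios 1.5 and 3 do not depend on the standard deviation, ICC or attrition.

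**What to change.** In the Primary outcome and Sample size calculation sections, replace the any-two-arms claim with power for each contrast: Intervention 1 v its own controls, Intervention 2 v its own controls, and, separately, the indirect Intervention 2 v 1 contrast. Compute these from corrected inputs. The design effect should match the planned patients per practice, the ICC should be described as within-practice correlation and not as a baseline-to-18-month correlation, and any gain from baseline adjustment should be stated with its assumed correlation.

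State how Medicare Local enters the tested time-by-group contrast: as a fixed area-by-time effect, as a random effect with an assumed variance, or as a main effect only. In the last case, say that controls are pooled across Medicare Locals and that the comparison is partly non-randomised.

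The cost is restated figures and a sentence or two on the model. Recruitment, allocation and data collection do not change. The sponsor would have to acknowledge that the differences detectable with 80% power may exceed 0.25 points, most of all for Intervention 2 v 1.
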